### Sample size

Sample size and power regarding group differences were calculated by a statistician. The aim of the study is to evaluate both implementation and effectiveness. The sample size calculation to evaluate implementation was based on the assumption that 15% more patients will receive neck-specific exercises in the intervention group (40% in the intervention group and 25% in the control group). The required sample size under individual randomization will be 150 patients in each arm. With 10 physiotherapy clinics (clusters) in each arm (a total of 20 clusters), intra-cluster correlation of 0.02 and a cluster size of 21 patients, a total of 420 patients will be recruited for 80% power and a significance level of 0.05. To ensure that enough people are in each group after dropouts, a total of 500 patients will be included, 25 patients from each cluster.

Sample size calculation to evaluate effectiveness was based on a clinically relevant improvement of 7% in the NDI, an effect size of 0.2 (Cohen’s f) or 0.4 (Cohen’s d), a correlation among repeated measures of 0.3, and the need for a total of 56 participants for 80% power and a significance level of 0.05. With an expected dropout rate of 20%, a total of 70 participating patients will be needed. The total number of patients may be more than 70 because patients will be recruited at each clinic.

Repeated-measure ANOVA or a linear mixed model will be used to examine changes in the patient-reported outcomes over time (i.e., at baseline and 3 and 12 months). The results will be compared with the results from the RCT studies [8, 12]. Patients who are included in both the intervention and control implementation groups and receive neck-specific exercises will be treated as one group in terms of the effect of the intervention. Analyses will be performed with parametric statistics if assumptions of normality are met, and otherwise with non-parametric statistics.

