#### Primary outcome

The primary outcome will be the proportion of patients with neck pain receiving neck-specific exercise during the intervention period. Data will be collected from each included physiotherapy clinic, based on each physiotherapist’s registered ICD-10 code (S134, S134A, S134B, S134C, T918, M501, M502, M503, M530, M531, M542) in the medical record.

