#### The effectiveness of NSEIT/NSE

Background data will be collected, including age, sex, symptom duration, and whiplash injury or other reason for neck pain.

The primary outcome measure that will be collected is neck-specific function as measured by the Neck Disability Index (NDI) [42].

The secondary outcome measurements will be pain intensity (current, average last week, worst pain last week) in the neck, head, and arm, and dizziness (current, average last week, worst dizziness last week) in the past week, using a numeric rating scale (NRS, score 0 to 10: 0 = no pain or dizziness, 10 = worst imaginable pain or dizziness) [43]; answers to questions about health-related quality of life; work ability measured with the Work Ability Score (WAS) reporting “current work ability compared to highest work ability ever” (score 0 to 10; 0 = cannot work at all, 10 = best work ability [44]; and patient’s improvement or deterioration over time, measured with an 11-point global rating scale (GRS: − 5 = vastly worse, 0 = unchanged, 5 = completely recovered) [45]. Any adverse events or negative effects will be registered at the 3-month follow-up.

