### Statistical analyses

All analyses will be conducted in collaboration with a statistician. Data will be analyzed according to intention to treat and supplemented with per protocol analysis. An analysis will be done of the missing data. Imputation methods may be used when deemed to have additional value. Subgroup analyses of age, gender, neck pain intensity, headache, and dizziness may possibly be performed.*Data regarding the implementation strategy* will be analyzed using a parametric t-test and a linear mixed model or repeated-measures ANOVA or the non-parametric Mann-Whitney U test and Kruskal-Wallis test, depending on the data. Analyses will evaluate differences between groups A and B and changes in variables over time.*Data regarding the effectiveness of NSEIT and NSE* will be analyzed with a linear mixed model or repeated-measures ANOVA or Kruskal-Wallis, depending on the data. NDI, pain intensity, headache, and dizziness will be evaluated as dependent variables with time as an independent fixed factor (baseline, 3 months, and 12 months after start of intervention). The results will be compared with the results from the RCT studies [8, 12].

The effect of neck-specific exercises in the present study for WAD grades II and III and for patients with other neck-pain disorders will also be evaluated and compared with the results in the RCT studies [8, 12].

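### The plan lets observed normality choose the primary analyses, and the rank fallback named for the NDI ignores the repeated measurements and does not estimate the planned effect

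*Protocol article*

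**What the plan says.** The Sample size section ends with a general rule: "Analyses will be performed with parametric statistics if assumptions of normality are met, and otherwise with non-parametric statistics". It exempts no outcome and gives no criterion.

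The Statistical analyses section makes the same choice twice. Implementation data are to be analysed by "parametric t-test and a linear mixed model or repeated-measures ANOVA or the non-parametric Mann-Whitney U test and Kruskal-Wallis test, depending on the data". Effectiveness data, with the NDI among the dependent variables and time as fixed factor, "will be analyzed with a linear mixed model or repeated-measures ANOVA or Kruskal-Wallis, depending on the data".

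In the same paragraph as the normality rule, the Sample size section says without condition: "Repeated-measure ANOVA or a linear mixed model will be used to examine changes in the patient-reported outcomes over time". It adds: "The results will be compared with the results from the RCT studies".

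The two primary outcomes are a proportion ("The primary outcome will be the proportion of patients with neck pain receiving neck-specific exercise during the intervention period") and a score ("The primary outcome measure that will be collected is neck-specific function as measured by the Neck Disability Index (NDI"). The first is sized on 40% versus 25%, the second on a 7% improvement in the NDI.

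**The concern.** A primary analysis should follow from the question. Here it follows from the shape of the data, and two sentences in one paragraph disagree on whether the mean-based model for the NDI is fixed or conditional.

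Three things are at stake.

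- The choice of primary analysis stays open until the data are seen.
- The rank test named for the NDI is built for independent groups, but the three NDI values come from the same patients.
- A rank test does not estimate a mean NDI change, which is what the 7% target and the comparison with the RCTs call for.

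**Working it through.** **1. The plan's own figures rest on means and proportions.**

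- Proportions, two-sided 5%, 80% power: (1.960 + 0.842)² × (0.40×0.60 + 0.25×0.75) / 0.15² = 7.85 × 0.4275 / 0.0225 ≈ 149, so 150 per arm as stated. A pooled-variance formula gives 152.
- Design effect: 1 + (21 − 1) × 0.02 = 1.40. Then 150 × 1.40 = 210 per arm, or 420 in 20 clinics of 21, as stated.
- NDI, within-patient repeated-measures ANOVA, three times, one group: λ = N × 3 × f² / (1 − ρ) = 56 × 3 × 0.04 / 0.7 = 9.6 on 2 and 110 degrees of freedom. Power is 78.7%, and 80% is reached at N=58, against 56 stated. Dropout: 56 / 0.8 = 70, as stated.

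The figures reproduce exactly or nearly so, on the mean and proportion scales.

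**2. Kruskal-Wallis on three measurements of the same patients.** The test takes the variance of a difference between two times as 2σ². With correlation 0.3 it is 2 × (1 − 0.3)σ² = 1.4σ². Under no change the statistic therefore behaves roughly like 0.7 times a chi-square on 2 degrees of freedom. The real type I error is about exp(−5.99 / (2 × 0.7)) = exp(−4.28) ≈ 1.4%.

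Simulation at N=56 and ρ=0.3 used normal data. For power it assumed a change complete by 3 months and then stable: means −0.283, 0.141, 0.141 SD, so f = √[(0.08 + 0.02 + 0.02)/3] = 0.2.

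| Test | Type I error | Power |
|---|---|---|
| Kruskal-Wallis | 1.6% | 60% |
| Friedman (respects the pairing) | 4.7% | 65% |
| Repeated-measures ANOVA | about 5% | 79% |

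Friedman repairs the error rate, but it too estimates no mean change.

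**3. Is the mean-based analysis adequate without normality?** The article gives no NDI mean, SD or skewness, so shapes were assumed.

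- For bounded scores in steps of 2 with mean 23 to 38, SD about 16 and skewness 0.31 to 0.83, the 95% t-interval for the mean covers 94–96% at n=56 and at n=420.
- For the paired change in skewed scores (SD 17.5), coverage is 94.5% at n=56, 95.0% at n=130 and 94.7% at n=400.

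**4. How often would a check trigger the switch?** Shapiro-Wilk at 5% stands in for the unnamed check. The NDI set is the patients who receive the exercise: 70 planned, or 250 × 0.40 + 250 × 0.25 = 162.5, about 163, if 25–40% of the 500 receive it.

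- Raw scores, bounded shapes of step 3: rejection in 16–90% of samples at n=56 and 57–100% at n=150.
- Baseline-to-3-month changes at n=163, SD 17.5, baseline means 25/35/45. Skewed shape: 85–88%, 31–38% and 15–21% in repeated runs. Normal shape cut at 0: 4–9%.

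The answer runs from rarely to nearly always, depending on assumptions the article does not settle.

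**5. The A–B comparison.** On clinic values there are 20 observations. At 40% versus 25%, ICC 0.02 and 21 patients per clinic, a normality check rejects in about 8% of simulated trials. Power is 75% for the t-test and 72% for Mann-Whitney, so little is lost. Mann-Whitney merely does not give the percentage-point difference directly. Patient-level 0/1 data are never normal, so a normality rule gives no useful guidance there.

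**The case against.** The fair case against runs as follows. No normality test is named, and for the planned models the assumption concerns residuals or changes, not raw scores. A reader might infer that several hundred bounded NDI scores make the switch nearly certain. The documents do not support that: step 4 shows low rejection for changes under some shapes, and the NDI set may be nearer 70 to 163 than 400.

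A reader might also infer that both primary outcomes would end with p-values and no estimate. That goes too far. A rank test does not forbid reporting means or proportions, and the implementation outcome is itself defined as a proportion. Nor does the large-sample argument carry over to 20 clinics.

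Finally, this is an article, an unseen analysis plan may settle the model, and the analysts are to be blinded to allocation.

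These points limit the size of the problem but do not remove it. The rule is stated, not merely left out, and an analysis plan that follows it inherits it. Blinding to allocation helps the A–B comparison, but not the NDI analysis, which pools both groups. The unconditional sentence on ANOVA or a mixed model favours the mean-based analysis, yet it conflicts with the Kruskal-Wallis option and with the rule that follows it.

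**Conclusion.** The point stands in limited form. The plan lets the observed distribution choose the analysis of both primary outcomes and contradicts itself on the NDI. If the NDI switch happens, the named test has type I error of about 1–2% and power of about 60%, where the planned analysis has 5% and 79%, and it does not estimate the mean change. These figures rest on N=56, f=0.2, ρ=0.3, normal data and a change complete by 3 months. Adequacy of the mean-based analysis rests on assumed NDI shapes.

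The probability of a switch cannot be fixed from the documents. For A versus B the harm is small: a rank test that does not directly give the difference the trial was sized on. The change is worth making, because following the rule can only worsen the NDI analysis and correcting it is cheap.

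**What to change.** Delete the normality rule in the Sample size section and the Kruskal-Wallis option for the NDI in the Statistical analyses section. Then state:

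- **NDI:** the primary analysis is the linear mixed model with time as fixed factor, whatever the distribution, reporting mean change with 95% CI.
- **A versus B:** the primary analysis is the clinic-level difference in proportions with 95% CI.
- **Sensitivity only, if residuals look poor:** a bootstrap CI for the NDI change and a permutation test over the 20 clinics.

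The cost is analysis wording. The sample sizes of 150 per arm and 420, and of 56 and 70, are unchanged, since they were derived on these scales.

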### Data management

All data will be monitored by the project team, independent on the study sponsor. To ensure participant confidentiality will a unique identifier be assigned to each participant after enrolment. Data will be stored on a secure website in the County Council of Sörmland. The website is password protected and will only be accessible by the project team. The results will be presented at the group level, and no connection to the individual person can be made. Outcome assessors and data analysts will be blinded for intervention allocation by having a researcher not involved in the analyses recode the groups using two random numbers.

### Dissemination policy

The results of the study will be disseminated through scientific papers, seminars and popular science reports and stakeholder. Authorship guidelines include actively contributing to scientific papers and professional writers will not be used.

### Timeline

Planning of the study began in January 2021. The trial started in April, 05, 2022 and we estimate that patients will be enrolled in the study in 2022–2023, with follow-up continuing until December 2024 (Fig. 3).

**Fig. 3 Fig3:**
[figure not shown]
Timetable for recruitment, implementation, and outcomes

## Discussion

Neck-specific exercises have been evaluated in two RCTs, showing reduced disability and neck pain in individuals with persistent WAD [8, 9, 12]. Access to internet-based treatment can shorten waiting time, enhance availability, and reduce costs. NSEIT was noninferior to NSE, and the exercise program can be delivered via internet with fewer visits to health care. The next step will be to implement NSEIT among physiotherapists in primary care. This pragmatic project is based on the RE-AIM framework and diffusion-of-innovation theory. At the staff and setting levels, our intent to evaluate the approach’s reach (the proportions of patients receiving NSEIT/NSE), and the adoption, implementation, and maintenance of the method. At the patient level, we plan to evaluate the effectiveness of NSEIT/NSE for patients with persistent WAD, the diffusion of NSEIT/NSE to other patients with neck pain, and the maintenance of results (long-term effectiveness). The project is important because it will increase our understanding of the factors that will promote implementation of NSEIT/NSE in primary care and because it will evaluate the effectiveness of the method. Results from this study will bridge the gap between research and clinical practice and guide large-scale implementation of NSEIT/NSE.

### Limitations

The limitations of the present study are related to the pragmatic approach. To study the implementation process and the adoption, diffusion, and maintenance of the NSEIT/NSE in clinical practice we could not follow as strict a protocol as in an RCT, which means we have less control over the study. The physiotherapists will select patients whose condition they have deemed to be improved by neck-specific exercises. Because all patients will be evaluated as one group, with no comparison with other treatments or exercise methods, threats to internal validity exist; that is, threats to confidence that the results are trustworthy. However, we will compare the results with the findings in our previous RCTs. Threats to the study’s external validity arise from the fact that only neck-pain patients and physiotherapy clinics that are interested in participating in the study will be evaluated. With these concerns in mind, the results can be generalized to physiotherapy clinics in primary care, as many different regions and physiotherapy clinics will participate in the study.

## Data Availability

Not applicable; the study corresponding to this manuscript is in the recruitment phase.

## Abbreviations

WAD: Whiplash-associated disorders
RCT: Randomized controlled trial
NSEIT: Neck-specific exercise with internet support
NSE: Neck-specific exercises at a physiotherapist clinic 2 times a week over 12 weeks
NDI: Neck Disability Index
EBM: Evidence-based methods
WAD ExerciseIT: The web-based information and exercise program directed at patients with WAD
Neck ExerciseIT: The web-based information and exercise program directed at patients with non-specific neck pain
ICD-10: The 10th revision of the International Statistical Classification of Diseases and Related Health Problems
EBPAS: Evidence-Based Practice Attitude Scale
PCS: Practitioner Confidence Scale
INERA: The Swedish web-based National Support and Treatment Services
NRS: Numeric rating scale
WAS: Work Ability Score
GRS: Global rating scale
ANOVA: Analysis of variance
